## Abstract

**Background:**

Emergency departments are chaotic environments in which complex, frail older persons living in the community and residential aged care facilities are sometimes subjected to prolonged emergency department lengths of stay, excessive tests and iatrogenic complications. Given the ageing population, the importance of providing appropriate, quality health care in the emergency department for this cohort is paramount. One possible solution, a nurse-led, physician-championed, emergency department gerontological intervention team, which provides frontload assessment, early collateral communication and appropriate discharge planning, has been developed. The aim of this Geriatric Emergency Department Intervention is to maximise the quality of care for this vulnerable cohort in a cost effective manner.

**Methods:**

The Geriatric Emergency Department Intervention research project consists of three interrelated studies within a program evaluation design. The research comprises of a structure, process and outcome framework to ascertain the overall utility of such a program. The first study is a pre-post comparison of the Geriatric Emergency Department Intervention in the emergency department, comparing the patient-level outcomes before and after service introduction using a quasi-experimental design with historical controls. The second study is a descriptive qualitative study of the structures and processes required for the operation of the Geriatric Emergency Department Intervention and clinician and patient satisfaction with service models. The third study is an economic evaluation of the Geriatric Emergency Department Intervention model of care.

**Discussion:**

There is a paucity of evidence in the literature to support the implementation of nurse-led teams in emergency departments designed to target frail older persons living in the community and residential aged care facilities. This is despite the high economic and patient morbidity and mortality experienced in these vulnerable cohorts. This research project will provide guidance related to the optimal structures and processes required to implement the model of care and the associated cost related outcomes.

**Trial registration:**

Australian New Zealand Clinical Trials Registration Number is 12615001157561. Date of registration 29 October 2015.

## Background

Across the developed and developing world the population is ageing. In Australia it is predicted that, compared to 2005 the proportion of the population over 65 years of age will increase from 13% to 24%, by 2036 [1]. With this increase, the demand on Emergency Department (ED) services by older persons living in the community or in residential aged care facilities (RACF) will increase [1–3]. A systematic review of 27 studies from around the world has demonstrated that the rate of transfer to EDs from RACFs is 0.1–1.5 transfers per RACF bed/year [4].

As a result of this ageing of the population it is imperative that the health care system develop safe models of care (MOC) that span both the community and hospital health care sectors. While the ED is uniquely designed to care for the critically ill or injured, it is often a suboptimal environment for the provision of care to the frail, older person [5, 6]. Prior research shows that older persons who develop an acute illness or who have an acute exacerbation of a chronic condition, have complex medical needs and the doctors and nurses who manage their initial care in the ED often have limited experience in geriatric medicine [7, 8]. Several studies have shown that this situation leads to: under-triage; higher rates of admission; delayed and fragmented care; longer stays in the ED; and unnecessary investigations and invasive interventions [9–19]. For patients from RACFs this is particularly true. During admission to hospital, patients from RACFs are at high risk of complications such as delirium, urosepsis, falls and death [20–22]. Patients from RACFs who develop an acute illness or an exacerbation of a chronic condition also suffer high rates of re-presentation to the ED and subsequent re-admission to hospital [2, 10, 12, 14].

Several studies indicate that a large percentage of frail older persons living in the community or RACFs express a preference for treatment in their home if appropriate [23, 24]. Despite this, approximately 60% of ED presentations lead to hospital admission [25, 26]. In an attempt to keep frail older persons at their place of residence during an acute illness, several MOC have been designed and tested. Broadly, the different MOC are divided into those that: i) provide in-home care or outreach of services from one service to another [12, 24, 27, 28]; ii) provide prioritisation or geriatric focused care in the ED [29–32]; or iii) support or enhance primary care [28, 33].

Interventions that focus on improving care in the ED for frail older persons living in the community or RACFs include, but are not limited to: nurse led discharge-planning [27, 32]; volunteers [31]; comprehensive geriatric assessment units; and care coordination programs [34]. It is unclear which MOC for frail older persons visiting EDs, will result in the best outcomes. Few randomised controlled trials of such interventions in the ED setting have been published [35]. Systematic reviews of studies that focus on these types of interventions have found that for the majority of older persons, ED interventions required further research as there is insufficient evidence to ascertain their impact. Crucially the majority of these studies exclude RACF residents, creating a serious evidence gap for this cohort [12, 30, 35]. Aldeen et al. [32] described an ED based geriatric nurse liaison MOC that shows promising results in decreasing hospital admission and safe discharge planning; however, it was limited to older persons living in the community in the American setting.

This study is part of a larger service evaluation project called the Care Coordination through Emergency Department, Residential Aged Care and Primary Health Collaboration (CEDRiC) project. The CEDRiC MOC has interconnecting elements in both the ED and the RACF to improve care for frail older persons and RACF residents in the ED and optimize primary health care. The aim of this article is to present the research protocol for a study that will evaluate the structures, processes and outcomes of an ED focused MOC aimed at improving care for frail older persons living in the community or RACFs who present to the ED with an acute illness.

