▪ In collaboration with GEDI Physician and university partners coordinate a program of research focused on the care of older persons in ED	▪ Ensuring discharge summaries are provided to all care providers e.g. GPs, RACF, primary carers, community services following acute ED care to allow seamless transition of care	▪ Create and edit clinical pathways and guidelines for best practice i.e. Delirium management
▪ Coordinate the aged care component of the ED staff development program in consultation with GEDI CNs and ED Nurse Educator	▪ Provide education for ED staff in evidence based care of the frail older person or RACF resident	▪ Leader in change management and lean thinking strategies
▪ Coordinate NP clinical practicum in the ED for NP candidates specialising in care of the frail older person or RACF resident to enhance skill base and knowledge of the ED setting. Skills obtained are translated into practice within the aged care service setting.	▪ Facilitate education/clinical exposure in the ED for NP candidates specialising in care of the frail older person or RACF resident to enhance skill base and knowledge of the ED setting.	▪ Negotiation of resource use in the ED
	▪ Establishment of rapid, direct referral pathways to specialised geriatric and palliative care departments	▪ Champion the GEDI model in strategic planning with senior staff and hospital administration
		▪ Collaborate and maintain research relationships
		▪ Participate in research and program audits
		▪ Administrator of GEDI team and budget
		▪ Collaborate with national and international geriatric focus groups
		▪ Liaise with other program directors/coordinators

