### Study design

Pragmatism will provide the philosophical paradigm for this mixed model evaluation research. This philosophical paradigm allows the researcher to focus on “what works” and provides solutions for problems utilising methods that best meet their needs and purpose [37]. The design will be underpinned by Donabedian’s structure, process and outcome evaluation of healthcare framework [38].

The three studies included in this protocol will aim to answer the following evaluative research questions:What is the effect of the introduction of the GEDI MOC on the outcomes of frail older persons living in the community or RACF who present to ED? (Outcomes include: rates of ED representation within 72 h and 28 days, mortality, ED and hospital LoS, time to referral and hospital admission rates).What structures and processes are required to deliver the GEDI MOC?Specifically:What are the experiences of staff in regards to the processes of the GEDI MOC?What processes pertaining to the GEDI MOC have affected the day to day operation of the ED, and how?What are the residents’ and carers’ experiences of the GEDI MOC?
What is the effect of the GEDI MOC on hospital and health service delivery costs?Specifically:What is the effect of the introduction of the GEDI MOC on per patient cost associated with ED and hospitalisation?What is the effect of the introduction of the GEDI MOC on preventing the costs associated with avoidable inpatient admissions?

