#### Study 1: Pre-post comparison of GEDI MOC in the ED

Study one is a quasi-experiment comparing outcomes for patients seen by the GEDI team to historical controls. As with all quasi-experiments, the disadvantage lies in the internal validity and risk of bias and this experiment will predominantly be affected by selection and historical control bias. Further to the selection bias and given the time difference between the pre and post intervention groups, events within the ED may influence the observed effects and lead to historical bias. Throughout the intervention a record will be made of any process or system changes that occurred within the ED during the GEDI team’s implementation [39]. These will be incorporated into the analysis.

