##### Samples

The study sample comprises frail older persons living in the community or RACF presenting to Nambour General Hospital ED during two time-periods:(i)Time 1: 1^st^ January to 31^st^ December 2012: prior to development of any aspect of GEDI MOC, and(ii)Time 2: GEDI MOC implementation: 1^st^ September 2015 to 31^st^ August 2016

The gap between these two time-periods was when the GEDI MOC was developing, partially staffed and supported and was, therefore, not operating at an optimal level.

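### Undated RACF elements of CEDRiC, if they began between 2012 and Time 2, could not be separated from GEDI in RACF residents, because the change log stops at the ED

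*Protocol article*

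**What the plan says.** The Background of the protocol article states: "This study is part of a larger service evaluation project called the Care Coordination through Emergency Department, Residential Aged Care and Primary Health Collaboration". It adds that "The CEDRiC MOC has interconnecting elements in both the ED and the RACF", and gives improvement of primary health care as a further aim. It gives no start date, content or list of facilities for the RACF elements.

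The Study design section asks: "What is the effect of the introduction of the GEDI MOC on the outcomes of frail older persons living in the community or RACF". The Samples section sets Time 1 as calendar year 2012, described as "prior to development of any aspect of GEDI MOC", and Time 2 as "GEDI MOC implementation: 1^st^ September 2015 to 31^st^ August 2016". Of the interval it says: "The gap between these two time-periods was when the GEDI MOC was developing, partially staffed and supported".

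On concurrent change, the opening of Study 1 says that "a record will be made of any process or system changes that occurred within the ED", and that these changes will enter the analysis. The Study 1 data analysis section adjusts for gender, age, triage score, season, day of week and time of presentation, and adds a linear date trend. Residence is not in that list, although the data collection section plans to identify RACF residents from home addresses. The Study 3 data analysis section compares savings from the before-after difference in admissions with the implementation cost of GEDI only.

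**The concern.** The article names a second component of its own programme, acting on part of its own sample, and then fixes its record of concurrent changes so that this component falls outside it. If the RACF elements came into operation after 2012 and were running in Time 2, RACF residents in Time 2 received GEDI plus those elements, and RACF residents in 2012 received neither. The period contrast in that group would estimate the combination, while the research question credits it to GEDI.

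Two results are exposed. In Study 1, RACF residents and community dwellers are analysed together, so part of any RACF-element effect would enter the pooled GEDI estimate. In Study 3, admissions avoided by the RACF elements would count as GEDI savings, with no cost of those elements on the other side. A service that wants to know what the ED team achieves, and at what cost, could be misled on both.

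**Working it through.** The article gives no figure on this point, so there is none to reproduce. The check asks whether the planned adjustments would remove an RACF-side change.

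**Inputs.** Samples section: Time 1 has 366 days, Time 2 has 366 days, and the gap is 365 + 365 + 243 = 973 days. The period midpoints are therefore 183 + 973 + 183 = 1,339 days apart, or 1,339 / 365.25 = 3.67 years. Study 1 data analysis: linear date trend and annual sinusoid. Setting section: 52,410 presentations a year, 18% over 70.

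**Method.** A least-squares model with one row per day, used as a linear stand-in for the Cox models: outcome = a + b × period + c × date + season. The true GEDI effect is set to zero and an RACF-side change of size 1 is added, so b shows how much of it is credited to GEDI. With period and date both in the model, the trend c is learned only from slopes within the two periods. Approximately, b = (difference in period means) − c × 3.67.

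| When the RACF-side change occurs | Difference in means | Trend c per year | b |
|---|---|---|---|
| Starts or phases in during the gap, full in Time 2 | 1.00 | 0.00 | 1.00 |
| Linear from January 2012 to August 2016 | 0.79 | 0.214 | 0.00 |
| Ramps from 0 to 1 across Time 2 | 0.50 | 0.50 | 0.50 − 0.50 × 3.67 = −1.33 |
| Starts 1 March 2016 | 0.503 | 0.707 | 0.503 − 0.707 × 3.67 = −2.09 |

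A change falling in the gap has the same pattern as the period indicator, so the trend removes none of it. The trend works only for a steady change over the whole span. A change during Time 2 makes it over-correct.

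The trend may also not survive. In this model the period indicator has a variance inflation factor of 41 with the trend and 48 with trend and season, against the article's removal threshold of 5.

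**Other safeguards.** The log would not record a change made in an RACF. Adding residence as a covariate would handle case mix but not this problem; separation needs an effect estimated by residence. For Study 3, no time-trend adjustment is stated for the admission difference.

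**Illustration, on assumed values.** Shift in the pooled admission rate = share affected × effect in those residents.

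- Share 5%: 0.05 × 10 points = 0.5 points.
- Share 20%: 0.20 × 10 points = 2 points.
- Presentations over 70: 52,410 × 0.18 = about 9,434 a year, so 0.5 points is about 47 admissions and 2 points about 189.
- Wider assumptions (share 10-30%, effect 2-10 points) give 0.2-3.0 points, about 19-283 admissions.

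**The case against.** The strongest reply is that the confounder is hypothetical. A reader might infer that the RACF elements were absent in 2012 and active in Time 2. The article says neither; it says only that no aspect of GEDI existed in Time 1. Nor does it support calling GEDI half of the programme, since no share or content is given for the other elements. This stands, and the point is therefore conditional.

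A reader might also take the nurse practitioner practicum in Table 1 ("Skills obtained are translated into practice within the aged care service setting") as the outside influence. It is not. Table 1 lists it as a task of the GEDI nurse consultant, and it also lists contact with RACF staff and pre-hospital communication as GEDI work. Effects through these routes belong to GEDI. This also means that the boundary between GEDI and the other elements is not sharp.

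It would be too strong to say that Study 1 credits the whole before-after difference to GEDI. The article concedes selection and historical bias and adjusts for patient factors, season, a trend and logged ED changes. The description is close to right only for the admission step of Study 3.

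Finally, a condensed article may leave the dates and content of a sister component to a fuller document. That is fair, and the missing dates alone would not be a finding. What remains is something the article does fix: a log limited to the ED, in a study whose own programme also works outside it.

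**Conclusion.** The point holds in conditional form. If the RACF elements of CEDRiC began between 2012 and Time 2, or were active only in Time 2, their effect on RACF residents cannot be separated from GEDI's by anything the article plans. A change completed in the gap passes in full (1.00) into the GEDI coefficient in the linear stand-in model, and a change during Time 2 can push the adjusted estimate the wrong way. If the elements were already in place in 2012 and unchanged, or did not operate in Time 2, there is no bias from this source.

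The size of the bias cannot be determined from the documents. The 0.5-2 point shift rests on an assumed share and an assumed effect and is illustrative only. The study remains feasible; what is affected is the attribution of the RACF and pooled estimates and of the Study 3 savings.

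**What to change.** 1. Extend the Study 1 change log to RACF and primary-care changes, with start dates and the facilities concerned.
2. Use the RACF flag already planned in data collection to estimate the Study 1 effect and the Study 3 admission savings separately for community dwellers and RACF residents.
3. Add a sensitivity analysis that excludes residents of facilities receiving the CEDRiC RACF elements, with the same facilities excluded in both periods so that case mix stays comparable. This should not be the main estimate, because it removes part of the group the study is meant to serve.
4. Label the RACF and pooled estimates as GEDI plus any concurrent CEDRiC elements. Present the community-dweller estimate as the least affected, not as unaffected, since the programme also aims at primary care.

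Cost: a facility list with dates, which address cleaning alone does not supply; a few extra model runs; and a change of wording. The separate estimates will be less precise than the pooled one.

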## Methods/design

### Study aims

The aims of the Geriatric Emergency Department Intervention (GEDI) MOC evaluative research project are to:Test the efficacy of the GEDI MOC by comparing the outcomes of all people aged 70 years or older who presented to a South East Queensland ED before the implementation of the GEDI MOC with those in the 12 months following implementation. Outcomes measured will be: rates of ED representation within 72 h and 28 days, mortality, ED and hospital LoS, time to referral, time to disposition and hospital admission rates;Describe and explore the structures and processes required for the effective delivery of the GEDI MOC;Conduct an economic evaluation of the GEDI MOC.

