##### Data analysis

Descriptive statistics will be used to describe the intervention and control groups including frequencies, percentages, appropriate measures of central tendency and distribution. We will use survival analysis to jointly model length of stay and disposition, with the four destinations as competing risks. We will use survival analysis for ED representations with out-of-hospital mortality as a competing risk. All models will adjust for the patient level factors of gender, age, triage score, season, day of the week and time of presentation. Pre-post designs are vulnerable to confounding by other changes over time that may be attributed to the intervention [39]. To control for this, we will include a linear trend (based on date) in all models to account for gradual changes that are not captured in the individual variables, e.g., experience of healthcare workforce. We will also adjust for season using a sinusoid with an annual cycle to control for the winter peak in morbidity [42]. The survival analyses will use Cox models and we will check the proportional hazards assumption. The models’ residuals will be checked for outliers and correlation over time. We will calculate Cook’s influential statistic and examine relatively large outliers. We will calculate the variance inflation factor and remove variables with a score above five on the basis that they are co-linear. The key outcome will be the mean effect of the intervention together with 95% confidence intervals. The results will be reported using the Strengthening the Reporting of Observational Studies in Epidemiology (STROBE) guidelines [43].

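### Study 1 sets one baseline year against one intervention year at one ED, so an ordinary year-to-year difference is aliased with GEDI and the 95% interval holds no between-year error

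*Protocol article*

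**What the plan says.** The Samples section of Study 1 defines the baseline as "Time 1: 1^st^ January to 31^st^ December 2012: prior to development of any aspect of GEDI MOC" and the intervention period as "Time 2: GEDI MOC implementation: 1^st^ September 2015 to 31^st^ August 2016". The time in between is left out: "The gap between these two time-periods was when the GEDI MOC was developing, partially staffed and supported". The Study aims likewise give the intervention side 12 months, comparing patients "before the implementation of the GEDI MOC with those in the 12 months following implementation". There is one site (Setting) and no concurrent control: "Study one is a quasi-experiment comparing outcomes for patients seen by the GEDI team to historical controls".

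The Study 1 Data analysis section adjusts every model for patient factors, a linear trend in date and an annual sinusoid, the last to "control for the winter peak in morbidity". Residuals are checked for correlation over time. Variables with a variance inflation factor (VIF) above five are removed. The result to be reported is stated as follows: "The key outcome will be the mean effect of the intervention together with 95% confidence intervals".

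The protocol does acknowledge history bias. The opening paragraph of Study 1 says that process and system changes in the ED will be recorded and used in the analysis.

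**The concern.** Each condition is observed in a single 12-month block containing one winter. How far ED length of stay, admission or re-presentation differs between two ordinary years cannot be estimated from one year per condition, so the interval for the period effect treats that variation as zero. A severe influenza season or a shift in case mix in either year goes straight into the GEDI estimate.

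Study 3 uses the same two periods and converts the before-after difference in admissions into savings. A chance difference between years could therefore be reported both as a clinical effect and as cost-effectiveness.

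**Working it through.** The protocol gives no sample size or precision figure for Study 1, so there is none to reproduce. What follows is an illustration on the admission rate, using a linear approximation to the planned Cox models.

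**Inputs.**
- Presentations: 52,410 × 18% = about 9,434 a year aged over 70 (Setting).
- Admission rate: 60%, a general figure in the Background, used here as an assumption; 40% gives the same standard error.
- Between-year SD of the admission rate: not given; assumed 0.5, 1 or 2 points.
- Daily design matrix from the protocol's dates: period indicator, linear date, annual sine and cosine.

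**Aliasing.** A shift of 2 points over the whole intervention year moves the GEDI coefficient by exactly 2.0 points, with or without the trend and sinusoid. The same shift in 2012 moves it by −2.0. No degrees of freedom are left for variation between years.

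**One bad winter.** Suppose June to August is 5 points higher in one year only (assumed). Without the trend, the GEDI coefficient moves by −1.26 points (2012) or +1.25 points (2016): the common sinusoid does not absorb it. With the trend, the shifts are +1.86 and −6.46. These also include misfit of the sinusoid carried across the gap by the slope, since equal excesses in both winters would shift the estimate by −4.60.

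**Collinearity.** The VIF of the period indicator given date and sinusoid is 48.2, and that of date is 48.4. Both are far above the cut-off of five, and the rule does not say which term goes.

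**Trend dropped.** Patient-level SE = √(2 × 0.24 / 9,434) = 0.713 points; half-width 1.96 × 0.713 = 1.4. True SE = √(0.713² + 2 SD²) = 1.00, 1.58, 2.92. False-positive rate = 2[1 − Φ(1.96 × 0.713 / true SE)] = 16%, 38%, 63%.

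**Trend kept, as planned.** SE = 0.713 × √48.2 = 4.95; half-width 9.7. True SE = √(4.95² + 2 SD²) = 5.00, 5.15, 5.70, which is 1%, 4% or 15% larger. False-positive rate = 5.2%, 5.9%, 8.9%.

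**Baseline 2009–2012, trend kept.** Patient-level SE is 1.265; half-width 2.5. The five year-weights in the period estimate are 1.215, 0.239, −0.736, −1.718 and 1, with sum of squares 6.03 (against 2.0 now). True SE = √(1.265² + 6.03 SD²) = 1.76, 2.76, 5.07.

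| Between-year SD (points) | 0.5 | 1 | 2 |
|---|---|---|---|
| Half-width, SD known | 3.5 | 5.4 | 9.9 |
| Half-width, rough, t on 2 df (4.30) | 7.6 | 11.9 | 21.8 |
| False-positive rate if year error is omitted | 16% | 37% | 62% |

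The 2 degrees of freedom are four pre-GEDI years less a fitted line. The VIFs fall to 5.04 (period) and 5.07 (date), still at the cut-off.

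**The case against.** The strongest reply is that the plan keeps a linear trend in all models. On that analysis the interval is so wide that the missing between-year component matters little: false-positive rates of 5.2% to 8.9%, not 16% to 63%. This stands. A reader might infer from the larger figures that the planned interval is grossly too narrow. The document does not support that, because those figures apply only if the collinearity rule takes the trend out.

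It can also be said that the authors know the weakness: they name history bias, log ED changes, model season and trend, and check residuals. That is fair, but none of these separates a year effect from GEDI. The trend covers smooth drift and the sinusoid an average winter. The log covers known local changes. A whole-year shift is absorbed by the period term, so residuals cannot show it.

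Third, more baseline years are no easy gain. A reader might take the 2.5-point half-width as the promised precision, but it omits the very variance at issue. With that variance included and estimated from four years, the interval can exceed the present 9.7 points. Extra years with a trend but no year-level error would do harm (16% to 62% false positives). Both objections stand and shape the fix.

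**Conclusion.** The point holds as a design limitation that should be addressed. The aliasing of year with GEDI, the absence of any between-year error and the VIF of about 48 follow from the protocol's own dates and model terms. They do not depend on an unseen analysis plan, because no plan can recover between-year variance from one year per condition.

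The size depends on the trend. If it is kept, the cost is mainly imprecision, with mild under-coverage. If it is removed under the protocol's own rule, the interval looks precise and its error rate may be several times nominal. The between-year SDs, the winter excess and the 60% admission rate are assumptions, and the linear model only approximates the Cox models, so the rates are illustrative.

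**What to change.** 1. In Samples, extend Time 1 to as many full, consistently coded pre-GEDI years as EDIS and HBCIS hold, for example 2009–2012 or longer. Leave Time 2 as it is. Extraction is already retrospective from routine databases (Study 1, Data collection), so no recruitment is involved.
2. In Data analysis, include a between-year error in the interval for the period effect, through a random year effect with small-sample degrees of freedom. Parts 1 and 2 must be adopted together.
3. Exempt the period and date terms from the VIF rule; even with 2009–2012 their VIFs remain about 5.
4. Show year-against-year contrasts among the pre-GEDI years as description only. None spans the gap between Time 1 and Time 2, so they are not matched to the GEDI contrast.
5. If earlier years are unavailable, state that the interval excludes between-year variation and give a sensitivity range over plausible SDs.

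The cost is a larger extract, manual address cleaning to identify RACF residents in the added years, checks of availability and coding consistency (the article does not say that linked data exist before 2012), and possibly a less favourable interval.
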